#### Lost to follow up

Lost to follow-up will be defined as not being able to ascertain a woman’s sexual assault status at 1 year. Our 6-month pilot study had less than 5% of participants moving or changing their phone numbers or e-mails without updating their information with the Registrar or contacting the researchers, and therefore being ‘lost to follow up’. The primary outcome for the present trial is at 1 year rather than at 6 month follow-up, and therefore we have doubled the estimated rate of lost-to-follow-up to 10%. We expect a loss of no more than another 15% at the end of the second year of follow-up. Our lost-to-follow-up numbers are reasonable based on recent estimates that less than 25% of students drop out of university by the end of their second year [87].

#### Compliance

Non-compliance (i.e., “no show”) will be defined as not receiving any brochures or not attending the education program. From our previous pilot studies, as many as 40-50% of women who completed baseline measures did not show up to receive their intervention which was scheduled at a later date. With a time-gap between baseline assessment and intervention, we were not able to reduce no-show below 40% with any techniques we tried in pilot tests. Therefore, for the present trial we will be pre-testing and randomizing on the same day, followed immediately by the (first or only) intervention session (and a meal) which should reduce non-compliance to near zero. In order to minimize attrition once the education intervention begins, enrollment into the trial will start close to the beginning of the term or immediately following the midterm period. We will also use incentives and reminder phone calls. The incentives for program/control session attendance include a ballot for a final study-end lottery of $300, a $25 movie pass, and a free lunch/dinner. To retain participants in the remaining education program units, reminder calls will be used, as well as, bonus points, refreshments, a cash lottery for each session ($50), a ballot for the study-end lottery for every session attended, a colorful clipboard filled with resources, a themed magnetic note board, and a completion certificate for full compliance. Using a lower level of incentives in our pilot study, we were able to attain full attendance at the educational program from more than 78% of participants.

Non-response on follow-up surveys will be defined as refusing to complete portions of or all secondary outcome follow-up surveys. We will use a number of procedures known to maximize response rates for follow-up surveys [86] such as confirmation of contact information at follow-up and multiple reminder calls, emails, and/or letters. Additionally, participants will be asked to provide long-term and collateral contact information at the post-intervention survey and at each subsequent follow-up survey. Specifically, they will be asked to provide primary and secondary email addresses, primary and secondary telephone numbers and their addresses during the summer (where applicable), and their future address if they are planning to move in the upcoming year. Participants also will be asked to provide the name, telephone number, and email address of at least two people who would be likely to know their whereabouts in the event that their contact information changes.

Our pilot studies also made it clear that attractive incentives must be in place so that participants stay in the trial for its full duration after the intervention is complete. We have chosen $30 gift certificates for survey completion based upon other studies in the literature [46,80] and our own pilots. We will also, based on participant feedback, be using web based surveys (with all appropriate security and privacy measures taken) for the follow-ups for this trial, which we found improved the ease with which women could participate and resulted in 100% 1 week and 89% 6 month completion ($20 incentive) for the 2007 pilot study. Moreover, the follow-up outcome surveys will take less than 30 minutes to complete which will maximize response rates [86].

The use of incentives is standard in psychological research and, increasingly, in clinical trials as long as the size of the payment cannot be seen to put ‘undue’ pressure on individuals to participate, and the sample is not a ‘vulnerable population’ e.g., [88-90]. Our pilot testing prior to the first program offering has confirmed that our lotteries (which keep down costs) are perceived positively by potential participants but that the size of the lottery ($500 total) does not work to induce an otherwise non-interested or unwilling person to consider participation. As such the $500 in lotteries is a useful incentive to strengthen existing interest without coercion. Our $25 movie passes for early survey sessions and $30 gift certificates for the follow-ups are well within the range clearly considered modest (<$100) and acceptable by authors publishing in *Contemporary Clinical Trial*[88]. With no incentives within a student population, our ability to recruit and retain participants in the longitudinal research would be extremely limited.

While cross-contamination effects are not likely to affect this kind of intervention [91], we will ask the women in the control arm at the 1-year follow-up the following questions: “Have you had conversations about sexual assault with other women?” “If yes, was this woman in the other longer program?” “How long was your conversation(s)?” “What did you talk about?” We will describe the amount of ‘contamination’ occurring and discuss its possible influence on the findings.

#### Training of facilitators and research assistants conducting interventions

A detailed manual has been written that provides instructions for the enhanced AAA sexual assault resistance program facilitators, including session materials, scripts, and trouble-shooting advice. The Principal Investigator will conduct a joint training program for all site facilitators in late summer in the intervention years of the trial. Training will include attendance at a WenDo Women’s Self-defense two-day Basic program and another day of specialized training by a certified WenDo instructor. Research Assistants will be trained by the Principal Investigator and the Trial Project Manager in site visits in September in both intervention years.

### Sample size considerations

The primary outcome is completed sexual assault (rape). Our 2006–2007 pilot randomized controlled trial of 214 students yielded the following cumulative incidences. For women in the control arm, the 3- and 6-month rates were 12% and 20%, respectively. For those in the sexual assault resistance education program, they were 6% and 11%, respectively. These figures correspond to a 50% relative risk reduction. This is comparable to the one previous study conducted by Hanson and Gidycz [49], which yielded a rate of 14% of rapes in their control arm and 6% in their intervention arm over a 3-month period, among women with no history of previous victimization. Given that the incremental incidence of sexual assault declines over time we estimate, for the purpose of sample size calculations, the 1-year rates to be 25% in the brochure arm and 17.5% in the educational program arm; a more conservative 30% relative risk reduction. Therefore, a sample size of 932 women (466 per group) will have 80% power to detect an absolute difference of 7.5% (25% versus 17.5% equals a 30% relative reduction) at a two-sided 5% level of significance. This is a meaningful reduction because it implies that for every 14 women who enroll in the program, 1 additional rape could be averted. Aside from power considerations, it is important to note that a sample of this size will yield a significantly positive trial when the observed difference between groups is as small as 5.4% (21.6% relative risk reduction). Although the intracluster correlation was calculated as −0.02 from our pilot study, +0.02 will be used to inflate the sample size with a design effect of 1.38 and a cluster size of 20 women. Assuming a lost-to-follow-up of 10% in the first year and 15% in the second year of follow-up, the total size of the trial will be 1716 women (932×1.38÷0.75).

### Statistical analyses

Analyses will be performed after all women have completed their one-year follow-up and at the end of the trial. Following the intention-to-treat principle, a participant will be included in the analysis if she is randomized. Using SAS software [92] the primary (and tertiary) analyses will compare the proportion of women with completed sexual assaults between groups using a Wald test from a log-binomial regression model (PROC GENMOD) that adjusts for compound symmetry (CS) clustering using generalized estimating equations. Covariates will be added to the model if differences among baseline characteristics are observed. In addition, a test for interaction will be performed using the above model to assess whether there is a differential treatment effect depending upon whether the women participated in the weekend versus weekday programs. Women who are lost to follow-up or drop out can affect the validity of the group comparison if (a) sexual assault is related to being lost or dropped and (b) it is differential between groups. Thus, baseline characteristics of women who are lost and drop out will be compared to women who complete the trial. In addition, the missing data mechanism will be formally tested [93] to determine whether it is Missing Completely at Random (MCAR) or is Missing at Random (MAR). Freedom from completed sexual assault will be compared between groups using Cox regression (PROC PHREG) with a robust sandwich covariance matrix to account for the clustering. Women who are lost to follow-up or drop out will have their data censored at the time of last contact.

For the secondary outcomes which are all continuous (or at least ordinal) longitudinal, repeated measures analysis of covariance (ANCOVA) will be used to compare intervention arms across the follow-up periods, adjusting for baseline scores on the instruments. Generalized linear models (PROC MIXED) will be used to correctly adjust the variance estimates for CS clustering. Recognizing that some of the instruments have ordinal responses, a rank-based ANCOVA will also be performed to assess congruency with the parametric analyses. For completeness in assessing the effect of missingness, two additional analyses will be conducted: (a) a ‘per-protocol’ analysis among participants who attend all sessions and respond to the 1-year SES-SFV questions; (b) multiple imputation of five data sets (PROC MI and MIANALYZE) using a discriminant function for binary outcomes and Markov chain Monte Carlo for continuous outcomes, assuming the missing data mechanism is MAR. The literature, for example [49], suggests that prior sexual assault can be a modifier with respect to the effectiveness of sexual assault resistance programs. Accordingly, program effects will be compared for women with and without sexual assault histories at baseline.

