**Discussion:**

The results of the trial will be used to produce a maximally effective sexual assault resistance education program that can be adopted by universities, to assess whether aspects of the program need to be strengthened, and also to indicate how long the effects of the program last and at which point in time refresher sessions may be necessary.

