### Previous trials of rape resistance programs

A systematic review of the literature confirms that despite the size of the ‘at risk’ population and the seriousness of health impacts of rape and sexual assault, a rigorous randomized controlled trial (RCT) of a rape resistance education program has not been conducted. Among the published studies of programs for female university students, only three have demonstrated a positive impact on completed rape rates. However, they have mixed effectiveness and lack the detail to allow a full evaluation of the processes and practices [46,47].

In their study, Hanson and Gidycz [48] found lower completed rape rates for women in the subsequent two months, but the benefit was only for women who had not been sexually victimized previously. This benefit for non-victimized women was not replicated in a later study that attempted to strengthen the program [49]. Increasing the focus on cognitive and emotional obstacles to resistance also did not improve the outcomes [50]. In an expanded 3-hour program with an increased emphasis on personal relevance to participants and changes expected to enhance processing of information, Gidycz et al. [51] reported a delayed benefit (occurring between 2 and 6 months following the program) for some women only. Women who took the program, and who were sexually assaulted but not raped in the two months after the program, were less likely to be assaulted in the next 4 months than were any other group of women. Gidycz et al. [46] expanded their program to two sessions and added a booster session at 3 months. The 7-hour program included a greater focus on problem solving related to reducing risk and self-defence training but was unable to produce any change in sexual assault outcomes. Orchowski et al.’s [47] addition of self-defence training was successful in producing short term (2 month) reductions in completion of sexual assault for women with and without a sexual assault history. Effects were not maintained 4 months later even with a booster session. Yeater et al. [52] tested the efficacy of reading a “skills-based” self-help book against a wait-list control with 110 college women and demonstrated a number of positive outcomes but no reduction in sexual assaults.

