#### Tertiary

To test the hypothesis that the intervention can: (a) reduce the one-year incidence of forced sexual contact and sexual coercion; (b) maintain the improvements in the primary and secondary aims for up to 24 months.

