### Outcome measures

#### Primary

Completed sexual assault (rape) will have occurred when a participant indicates she has had at least one experience of sexual intercourse (oral, anal, or vaginal) that was threatened, forced, or drugged (completed, not attempted) in the period between the previous outcome measurement and the present; answered ‘once’ or more to any of 9 questions (involving oral sex, vaginal penetration, and/or anal penetration “without consent” when the woman was “too drunk or out of it to stop what was happening”, was threatened with physical harm to herself or others she cares about, and/or was forced, “for example holding me down with their body weight, pinning my arms, or having a weapon”) on the *Sexual Experiences Survey* - *Short Form Victimization* SES-SFV, [71]. Month of occurrence will be recorded to permit time-to-event analyses. Previous versions of the SES have been used in large university, college, and community samples, and it is considered the gold standard. Responses on the scale are stable across administrations. Test-retest reliability is very high, and responses are also comparable to those received through interviewing women [72]. Concurrent validity has been demonstrated using correlations between sexual victimization as measured with the SES and variables predicted to be affected or influenced by that victimization, for example, hostility toward men [73,74]. Construct validity has been demonstrated when women’s descriptions of sexual experiences were rated by interviewers (on the items of the SES) and compared to the women’s own responses on the SES [75].

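### For completed sexual assault, the named 24-month analyses do not separate a lasting program effect from a first-year difference carried forward

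*Protocol article*

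**What the plan says.** Under Aims, Tertiary, hypothesis (b) is that the intervention can "maintain the improvements in the primary and secondary aims for up to 24 months". The abstract's Discussion says the results will be used, among other things, "to indicate how long the effects of the program last and at which point in time refresher sessions may be necessary", and the main Discussion repeats this.

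For completed sexual assault, Statistical analyses names two methods:

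- A log-binomial GEE model, in which "the primary (and tertiary) analyses will compare the proportion of women with completed sexual assaults between groups using a Wald test". On timing: "Analyses will be performed after all women have completed their one-year follow-up and at the end of the trial".
- A time-to-event comparison: "Freedom from completed sexual assault will be compared between groups using Cox regression (PROC PHREG) with a robust sandwich covariance matrix".

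No second-year comparison, arm-by-period term or time-varying hazard ratio is named. Outcome measures, Primary, counts an assault reported "in the period between the previous outcome measurement and the present" and records the month of occurrence, so the data for a period-specific analysis will exist.

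**The concern.** Maintenance asks whether the arms still differ in new assaults after the first year. A proportion accumulated from randomization to month 24 contains every first-year event. A difference won by month 12 therefore remains at month 24 even if the arms are identical from then on. A Cox model with only an arm term averages the effect over the whole follow-up and has the same limitation.

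Loss of effect is a possibility the article itself raises. Of one earlier program with a two-month benefit it says: "Effects were not maintained 4 months later even with a booster session". At stake is whether the trial can answer its own question of how long the effect lasts and when a refresher may be needed.

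**Working it through.** **Inputs** (Protocol article, Sample size considerations): one-year rates 25% and 17.5%; two-sided 5% level; 80% power; 466 per group; design effect 1.38; 25% total loss by month 24; total 1716. The article gives no second-year incidence and says only that incremental incidence declines. I assume a risk q of 5% to 25% among women not yet assaulted at month 12.

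**The plan's own figure.** Two proportions, pooled variance, no continuity correction, 25% v 17.5%: 466 per arm, power 0.800. Design effect 1 + 19 × 0.02 = 1.38. Total 932 × 1.38 ÷ 0.75 = 1714.9, consistent with 1716. The sample size is correct. The effective number per arm at month 24 is 1716 × 0.75 ÷ 1.38 ÷ 2 = 466.

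**Scenario: planned effect in year 1, none in year 2.** The 24-month proportions are 0.25 + 0.75q (control) and 0.175 + 0.825q (program). For q = 10%:

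- Control 0.25 + 0.075 = 0.325; program 0.175 + 0.0825 = 0.2575; difference 0.0675; RR 0.792.
- Null standard error √(2 × 0.29125 × 0.70875 ÷ 466) = 0.02977; alternative standard error √((0.325 × 0.675 + 0.2575 × 0.7425) ÷ 466) = 0.02968.
- Power = Φ((0.0675 − 1.96 × 0.02977) ÷ 0.02968) = Φ(0.31) = 0.62.

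**Cox model, same scenario.** Year-1 hazard ratio ln(0.825) ÷ ln(0.75) = 0.669. Year-1 events 466 × 0.425 = 198; year-2 events 466 × 1.575 × 0.10 = 73. The event-weighted log hazard ratio is (198 ÷ 271) × ln(0.669) = −0.294, so the overall hazard ratio is 0.75. Schoenfeld's formula gives power 0.68; a log-rank simulation (4000 runs, monthly times, 466 independent women per arm) gave 0.67.

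| Assumed q | 24-month proportions | RR | Proportion significant | Overall HR | Cox significant |
|---|---|---|---|---|---|
| 5% | 28.8% v 21.6% | 0.75 | 71% | 0.71 | 74% |
| 10% | 32.5% v 25.8% | 0.79 | 62% | 0.75 | about 67% |
| 15% | 36.3% v 29.9% | 0.82 | 54% | 0.77 | 62% |
| 20% | 40.0% v 34.0% | 0.85 | 48% | 0.79 | 57% |
| 25% | 43.8% v 38.1% | 0.87 | 41% | 0.81 | 52–53% |

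In the same simulations, a test restricted to months 12–24 among women event-free at month 12 rejected in 4.6% to 5.4% of runs, which is the nominal level.

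**Precision of a second-year estimate.** With 10% incidence in both arms and 466 per arm, the standard error of the log RR is √(2 × 0.9 ÷ 46.6) = 0.197. The 95% interval is the estimate multiplied or divided by exp(1.96 × 0.197) = 1.47. Power for a sustained 30% reduction (10% v 7%) is 31% among women event-free at month 12 and 38% among all women.

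**The case against.** Several objections are fair and limit the point.

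- **The window is inferred.** Statistical analyses does not call the 24-month proportion cumulative, and the outcome definition is per survey interval. An interval proportion could be meant. The cumulative reading is more natural, because the primary aim is one-year incidence, the sample size section works with cumulative incidences, and the final analysis is not restricted to year 2. It remains a reading.
- **Period terms are often left to the analysis plan.** True in general. Here, though, the article fixes the tertiary test, and as worded that test answers a different question from aim (b).
- **The cumulative test is not wrong in itself.** In the scenario above, 32.5% v 25.75% is a real difference in 24-month risk. The 62% is not a false-positive rate for that quantity.

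Four stronger readings are tempting but unsupported. A reader might infer that a faded program would be declared maintained; no section equates significance at 24 months with maintenance, and the one-year result would be reported too. A reader might infer that earlier programs in general faded; Previous trials of rape resistance programs describes one effect lost over time and another program with a delayed benefit between 2 and 6 months in some women. A reader might see waning in the sponsor's pilot (12% v 6% at 3 months, a 50% reduction; 8% v 5% at 6 months, 37.5%). With 214 women, assuming equal thirds and the two program arms pooled, the RRs are roughly 0.50 (0.20 to 1.2) and 0.63 (0.22 to 1.8), so no decline is shown. Finally, a reader might want a second-year test as the deciding one; at 31% to 38% power it would usually miss true maintenance.

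**Conclusion.** The point holds for completed sexual assault only. The named analyses do not answer the maintenance part of tertiary aim (b), nor the question of how long the effect lasts. On the cumulative reading, the 24-month proportion would be significant in about 41% to 71% of trials with no second-year effect, and the overall Cox comparison in about 52% to 74%. These figures rest on the planned first-year rates, the planned design effect and loss, and an assumed second-year incidence of 25% down to 5%; the conclusion is the same across that range. If interval proportions were intended, one sentence saying so would settle most of it.

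The primary one-year test is untouched. Maintenance of the secondary scores is also unaffected, since these are analysed across follow-up periods by repeated-measures ANCOVA. The change should be made, but it does not threaten the main result.

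**What to change.** 1. State the window of the 24-month proportion and keep it as the comparison of 24-month incidence.
2. Add risk ratios with confidence intervals for 0–6, 6–12, 12–18 and 18–24 months, and pooled for 12–24 months, from one log-link GEE with an arm-by-interval term. Include all responding women in each interval, counting a woman again if she reports a further assault. This avoids selecting on being assault-free at month 12, which is a post-randomization condition.
3. Add an arm-by-period term to the Cox model. Its second-year part does condition on being event-free, so it supports item 2 and does not replace it.
4. Base statements on duration of effect and refresher timing on these estimates and their intervals, not on significance of the cumulative result.
5. State that a non-significant 12–24 month ratio is not evidence of fading.

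The cost is analysis wording and some additional output; no new data are needed. The price is precision: at 10% incidence the pooled second-year interval runs from the estimate divided by about 1.47 to the estimate multiplied by about 1.47, and the plan should say so.

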(c) Knowledge of effective rape resistance strategies will be measured by identification of a greater number of forceful physical and forceful verbal strategies in response to threatening hypothetical situations (*Resistance measure*, [79]) and real situations (items requesting details following sexual assaults experienced, questions added to SES items, [48]). Testa et al.’s [79] measure follows a scenario depicting an interaction where the participant is on a date with “an attractive man” (p. 666). These items about the participant’s “intended behaviour” break down into 3 subscales: direct-resistance, polite-resistance, and passive-response. The direct-resistance subscale, which is our focus, has high internal consistency ranging from 0.89 to 0.94 and validity demonstrated by the authors. Additional, added questions, “If a man I knew (e.g., a date) tried to force me to have sex with him when I didn’t want to, I would …”, If a stranger tried to force me to have sex with him when I didn’t want to, I would …” were pilot tested to ensure clarity and consistency of coding of responses. Scoring is based on Ullman’s [45] study of the tactics used by women who avoided completed rape and has high inter-rater reliability (Cohen’s kappa > 0.90).

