(d) Ability to realistically assess risk of harm in hypothetical scenarios where acquaintance sexual assault is likely will be measured using the: (1) *Risk perception* questionnaire [79]. Using the same scenario with “an attractive man” as the strategies measure above, the risk perception measure presents statements of 10 possible outcomes, 4 positive and 6 negative. The participants answer on a 7-point scale, from *not at all* to *very likely*, what they perceive the outcome of the interaction will be. Internal consistency is in excess of 0.85 by Cronbach’s alpha; (2) *Risk Perception Survey* (RPS) [80]. Two vignettes, one based on a stranger and one on an acquaintance situation “were designed to incorporate risk factors identified in the literature and included … clear risk factors and ambiguous risk factors” (p. 162). Participants are asked to identify the line number at which they feel uncomfortable (identify risk) and the point at which they would leave (take action). Higher scores indicate toleration of higher risk in the situation. These are the only measures available and once completed cannot be used again due to familiarity with the scenarios. As such, this outcome can only be measured 3 times (Testa’s once; Messman-Moore’s twice, once each for the stranger and acquaintance versions). The timing of measuring this outcome is spread out across the first year of follow-up.

(e) Beliefs and attitudes about rape will be measured by endorsement of rape myths (*Illinois Rape Myth Acceptance Scale* IRMA-SF,[81], and misinformation about the causes of rape (*Perceived Causes of Rape Scale* PCOR,[82,83]. The IRMA has the best psychometric properties of any rape myth scale, having excellent criterion-related validity (correlations with measures of sexism and hostility toward women) and reliability. Internal consistency is high (Cronbach’s alpha > 0.82). The PCOR “provides [an] assessment of a range of people’s beliefs about the causes of rape that are not exclusively rape myths” [83], p. 228. This 32-item instrument provides participants with the stem “Rape is caused by ....” and they answer how much they agree with a list of causes. Our focus is on the *Female Precipitation* subscale which has the best internal consistency. Test-retest reliability of 0.87 is also good.

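### The baseline-adjusted repeated-measures ANCOVA set for every secondary outcome cannot be run for risk detection (d), and for real-life resistance in (c) it would compare arms only among women reporting an assault

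*Protocol article*

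**What the plan says.** All references are to the protocol article.

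- **Statistical analyses.** One rule covers the secondary outcomes: "For the secondary outcomes which are all continuous (or at least ordinal) longitudinal, repeated measures analysis of covariance (ANCOVA) will be used" to compare arms across the follow-up periods, "adjusting for baseline scores on the instruments". A rank-based version is added as a check. No secondary outcome is excepted.
- **Outcome measures, Secondary (d).** Risk detection uses two instruments. The first is a questionnaire on a dating scenario: "the risk perception measure presents statements of 10 possible outcomes, 4 positive and 6 negative", each rated on a 7-point scale. The second is a survey with a stranger vignette and an acquaintance vignette, scored by line number. On reuse the text says "These are the only measures available and once completed cannot be used again due to familiarity with the scenarios". It concludes that "this outcome can only be measured 3 times": the questionnaire once and each vignette once. On timing: "The timing of measuring this outcome is spread out across the first year of follow-up".
- **Outcome measures, Secondary (c).** Knowledge of resistance strategies is measured in hypothetical situations and also in "real situations (items requesting details following sexual assaults experienced, questions added to SES items".
- **Aims, Tertiary (b).** The program is to "maintain the improvements in the primary and secondary aims for up to 24 months", with no exception for (d).

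**The concern.** The model needs two things of each outcome: a baseline score on the same instrument, and scores on that instrument at more than one follow-up. The description of (d) rules out the first, and the second is available at most as two different vignettes. The stated analysis therefore cannot be carried out for one of the five secondary hypotheses, and a replacement would have to be chosen later, possibly after data are seen. The 24-month aim covers (d) by its wording, although no measurement of (d) is planned after the first year.

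The real-situation part of (c) has a different problem. A woman who reports no assault has no tactics to score. Applying the common model there compares the arms within a subset formed after randomisation by an event the program is designed to make rarer. The women who remain in that subset need not be comparable between arms.

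The Secondary outcomes section presents (a) to (d) as the intermediate steps through which the program works and as the basis for revising it. A selected comparison could misdirect that revision.

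**Working it through.** **1. Outcome (d) against the model**

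| Measurement | Metric | Planned uses | Same-version baseline | Score after year 1 |
|---|---|---|---|---|
| Questionnaire | 10 statements, 7-point ratings | 1 | none | none |
| Stranger vignette | line number | 1 | none | none |
| Acquaintance vignette | line number | 1 | none | none |

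Using one measurement as a baseline does not rescue the model. The text places all three in follow-up. A measurement moved to baseline would be spent, and it would not be the baseline score of the others. The two vignettes share an instrument and a metric, so a two-occasion model could be fitted to them. It would still lack a baseline score, and any change between occasions would mix time with the switch from one vignette to the other.

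**2. Planning figures reproduced**

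Inputs from Sample size considerations: 25% and 17.5% at one year, two-sided 5%, 80% power, intracluster correlation 0.02, cluster size 20, losses of 10% and then 15%.

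- Per arm, with pooled variance under the null and no continuity correction: n = [1.960·√(2·0.2125·0.7875) + 0.842·√(0.25·0.75 + 0.175·0.825)]² / 0.075² ≈ 466, so 932 in total, as stated.
- Design effect: 1 + 19 × 0.02 = 1.38, as stated.
- Total: 466 × 1.38 / 0.75 = 857.4, rounded up to 858 per arm, so 1716, as stated.

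**3. Women with a real-situation score at one year**

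Assumption: only completed assault triggers the items. Count = 858 × share followed × assault rate.

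| Loss | Control (25%) | Program (17.5%) |
|---|---|---|
| 0% | 214.5 | 150.2 |
| 10% (planned for year 1) | 193.1 | 135.1 |
| 25% | 160.9 | 112.6 |

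At 10% loss that is about 328 women: 21% of those followed and 328 / 1716 = 19% of those randomised.

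**4. How large the selection effect could be**

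This is a worst-case bound, not an estimate. Suppose the program has no effect on tactics and averts a share q of would-be assaults. Suppose also that tactic scores are normal among would-be assaulted women, and that which assaults are averted depends wholly on the score. The mean of those remaining then shifts, up or down, by φ(z₁₋q)/(1 − q) standard deviations.

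- At the planned q = 0.30: 0.348 / 0.70 = 0.50 SD.
- At q = 0.10, 0.20 and 0.50: 0.19, 0.35 and 0.80 SD.

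**The case against.** The strongest reply is that the analysis sentence is a one-line summary in a condensed article. Dropping an unavailable covariate for one outcome is routine analysis-plan detail, and the limit on (d) is disclosed openly. Part of this stands: nothing is hidden, and the repair is small. But the article is not silent. It says all secondary outcomes are longitudinal, names the model and names the covariate, and its own description of (d) contradicts that. The 24-month aim conflicts with the same description.

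On (c), it can be said that no sentence plans an arm test among assaulted women specifically, and that the added items may follow any experience reported on the survey. The first is true; the comparison arises from applying the general rule to (c). The second would enlarge the subset, but it would still be defined by events after randomisation that the program aims to reduce.

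A reader might infer more than the article supports:

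- **That (d) has no valid analysis at all.** Randomisation makes an arm comparison at each single time point valid without a baseline score; baseline adjustment mainly adds precision.
- **That (d) uses three unrelated instruments.** The two vignettes are versions of one.
- **That the direct-resistance scale in (c) is also single-use.** It shares a scenario with the (d) questionnaire, but the reuse limit is stated only for (d). Section (c) also lists added questions about a known man and a stranger, with no stated limit.
- **That the real-situation comparison would come out reversed.** This is possible, but nothing in the article shows it.

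**Conclusion.** The point holds in two parts.

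For (d), the stated model cannot be run and maintenance to 24 months cannot be tested. This follows from the article's own text and needs no assumption.

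For the real-situation part of (c), an arm comparison under the stated rule is open to selection bias of unknown size and direction. The figures of about 193 and 135 women rest on the planning rates, 10% loss, and completed assault as the only trigger. The 0.50 SD figure is an upper bound under the extreme assumptions listed with it, and the likely bias may be much smaller.

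The primary outcome, its test and the sample size are untouched, and the hypothetical-situation measures of (c) are defined for every randomised woman. Severity is moderate.

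**What to change.** 1. **Statistical analyses:** except (d) from the repeated-measures rule. State that each of its measures will be compared between arms at its single time point, adjusted for clustering and without a same-instrument baseline score.
2. **Aims, Tertiary (b):** exclude (d) from the 24-month claim.
3. **Outcome (c):** base the test on the hypothetical-situation measures. State whether the direct-resistance scale is repeated; if it is not, the exception in item 1 should cover it too.
4. **Real-situation responses:** report them descriptively by arm, with the number of women contributing and the experiences that trigger the items, and without a formal test.

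Other covariates for (d), and any multiplicity rule across its three measures, are choices for the analysis plan.

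The cost is wording, including one change to a stated aim, with no new data collection. Outcome (d) loses a 24-month claim that its data could not support, and the real-situation items lose a formal test. The change should be made before any arm comparison of the one-year data.
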